# A Randomized Placebo-Controlled Trial of Combination Therapy With Post-triple-antibiotic-therapy Fecal Microbiota Transplantation and Alginate for Ulcerative Colitis: Protocol

**DOI:** 10.3389/fmed.2022.779205

**Published:** 2022-02-22

**Keywords:** ulcerative colitis, alginate, fecal microbiota transplantation (FMT), double-blind randomized controlled trial, antibiotic-FMT, placebo-controlled clinical study

## Abstract

**Background:**

Fecal microbiota transplantation (FMT) has been widely performed for ulcerative colitis (UC) treatment at the clinical trial stage. Previous reports have used multiple FMT methods to enhance the colonization of healthy donor microbiota in the recipient's intestines. FMT following triple antibiotic therapy with amoxicillin, fosfomycin, and metronidazole (A-FMT) is not only effective but also requires only one FMT, which improves dysbiosis caused by reduced Bacteroidetes diversity in patients with UC. Alginate and its derivatives have the potential to induce the growth of intestinal bacteria including Bacteroides members and produce short-chain fatty acids (SCFAs), which are beneficial in regulating overactive autoimmunity. Our trial aims to investigate whether post-intervention with alginate, which can improve the intestinal environment, will enhance the therapeutic effect of A-FMT in UC and increase the long-term remission rate.

**Methods and Analysis:**

This trial is a double-blinded, randomized, placebo-controlled, parallel assignment trial. Patients with UC and fecal donation candidates will undergo strict screening before being involved in the trial. Eligible patients are randomly divided into two groups: one group will drink one bottle of alginate twice a day for 8 consecutive weeks after A-FMT, while the other group will take a placebo instead of the alginate drink. The primary endpoints are the changes in the Total Mayo Score at 8 weeks after study initiation and A-FMT from baseline. The secondary endpoint is the comparison of clinical features, microbiota, and metabolomic analysis before and after 8 weeks of study food intake. Changes at 6, 12, 18, and 24 months after A-FMT will be assessed. Finally, a subpopulation analysis of the relationship between patients and donors is an exploratory endpoint.

**Discussion:**

The FMT post-treatment used in this study is an oral alginate drink that is easily accepted by patients. If the regimen achieves the desired results, it can further improve the A-FMT regimen and provide evidence for clinical practice guidelines for UC.

**Clinical Trial Registration:**

https://jrct.niph.go.jp/latest-detail/jRCTs031200103, identifier: jRCTs031200103.

## Introduction

Although advances in ulcerative colitis (UC) drug treatment regimens have been made, 20–25% of patients choose a surgical intervention due to resistance or intolerance to drug treatment, which can cause pain and inconvenience to patients (1). To date, the pathogenesis of UC is not completely understood, and is only known to be the result of autoimmune processes and genetic and environmental factors; however, patients with UC commonly show decreased diversity and richness in the intestinal microbiota, resulting in dysbiosis (2, 3). Dysbiosis is thought to contribute to the development of aberrant immunological responses in inflammatory bowel disease (IBD) (4).

Fecal microbiota transplantation (FMT) is a minimally invasive therapeutic approach that involves transplanting intestinal microbiota from healthy donors to restore the normal intestinal microbiota functions in patients with disease-related dysbiosis. The implementation of FMT to treat UC is rapidly attracting the attention of the public (5, 6). Randomized clinical trials have assessed the use of multiple FMT operations for enhancing the colonization of the intestinal microbiota from healthy donors (7–10). The clinical remission rate of patients receiving FMT reached an average of 42.1% (11). However, the methods outlined in the above reports are difficult to manage and implement in actual clinical practice.

FMT following triple antibiotic therapy with amoxicillin, fosfomycin, and metronidazole (A-FMT), a method used by our team, is simple to operate because it only requires one FMT *via* colonoscopy followed by administration of antibiotics for 2 weeks. The combination antibiotic therapy consisting of amoxicillin, fosfomycin, and metronidazole (AFM) was modified for amoxicillin, tetracycline and metronidazole (ATM) therapy to reduce the adverse events caused by tetracycline. The efficacy of these combination antibiotic therapies (AFM, ATM) in treating patients with UC was previously reported (12, 13). We employed AFM as antibiotic pre-treatment to enhance reprogramming of the host intestinal microbiota by increasing the donor microbe colonization (14) and to achieve synergistic effects with FMT. We previously reported that A-FMT contributed to the recovery of the Bacteroidetes composition, which is associated with clinical responses and UC severity (15). It has also been observed that Bacteroidetes species components in clinical responders treated with A-FMT remarkably resembled those of their donors (16). These results indicate that A-FMT can effectively transplant the Bacteroidetes cells which is lost as UC activity progress (17) in fecal specimens from the donor to the intestinal environment of the recipient, which is parallel to the clinical improvement of UC. Furthermore, the high average clinical remission rate (43.8%) was observed in patients at four weeks after administering A-FMT comparing to previous reports with conventional FMT methods (42.1%) (15, 18). Although A-FMT exhibited obvious advantages compared to AFM monotherapy in our long-term clinical study, the remission rate gradually declined to 18.2% within 24 months (18). Wei et al. reported that intervention with pectin, a soluble dietary fiber extracted from apples, after FMT can preserve the diversity of the intestinal microbiota of patients with UC, providing results similar to those of donors (19). We speculate that FMT combined with post-interventions to maintain the diversity of the intestinal microbiota may improve the efficacy of FMT in UC treatment.

Alginic acid is a soluble dietary fiber polysaccharide that is widely distributed in the cell walls of brown algae in the form of alginate (20). Previous reports have found that alginate oligosaccharides have various activities, such as anti-inflammatory activity (21), antifungal activity (22) and immunomodulatory activity (23). Besides, alginate not only has a protective function on mucous membranes of the upper gastrointestinal tract (24), but also ameliorated the symptoms of experimental colitis and inflammatory responses (25). Mirshafiey et al. have also verified that alginate can be used as a potential treatment option for UC in both acute and chronic phase by rat models (26, 27). Furthermore, alginate and its derivatives can improve the growth of intestinal bacteria and can be fermented by human gut bacteria to produce short-chain fatty acids (SCFAs), which are beneficial to the intestine (28–30). A meta-analysis showed that clinical improvements in IBD are associated with the abundance of fecal microbiota and the enrichment of SCFA-producing anaerobes (31). Therefore, the aims of our study are to determine whether post-intervention with alginate can increase the diversity of microbiota to enhance the therapeutic effect of A-FMT in UC and delay the loss of microbiota diversity to improve the long-term remission rate. To our knowledge, this is the first randomized controlled study of the relationship between alginate and UC therapy.

## Methods and Analysis

### Study Design and Patients

This double-blinded randomized, placebo-controlled, parallel assignment trial will be conducted at Juntendo University Hospital (Tokyo, Japan). The study will be conducted until December 31, 2024 and is expected to involve 60 patients with UC. Diagnosis of UC will be established based on standard clinical, endoscopic, and histological findings (32) and both hospitalized patients and outpatients will be included. To be eligible, patients must be diagnosed with active UC and meet the requirements of obtaining a Total Mayo Score of 3–10 (7, 9, 10) and a Sum Endoscopic Mayo Score of 2 or above. All patients will be over 20 years old and competent enough to provide informed consent. There are no restrictions on gender.

To ensure the safety of patients, rigorous screening of patients will be performed. If the patient has serious illness, pregnant women, or has received local therapy, etc. will not be included in our experiment. The detailed exclusion criteria for this study are listed in Table 1.

**Table 1 T1:** Exclusion criteria for patients with UC.

Informed consent not provided
Infectious enterocolitis
Receiving local therapy
Serious disease, such as liver disease, kidney disease, heart disease, or other serious complications
Autoimmune disease
Pregnant women and all cases with the possibility of pregnancy
Allergic diseases
Antibiotic therapy in the past 3 months
Any other cases judged inappropriate by the responsible researcher

*UC, Ulcerative colitis*.

### Donors

To understand the health status of the donors and reduce additional costs, we will conduct a preliminary medical inquiry and physical examination of the donor candidates. As dysbiosis is correlated with neuropsychiatric disorders including depression and autism (gut-brain interaction) (33, 34), the Hamilton Depression Scale (HAMD) and Neuropsychiatric Inventory (NPI) will be used to assess psychiatric symptoms (Table 2A). There are no restrictions on gender. In addition, to minimize the risk of infection transmission, the donor candidates who have passed the preliminary screening will undergo fecal and blood tests. Donor candidates who test positive for any of the items in Tables 2B, 2C will be excluded. Candidates who pass the above rigorous screening will become eligible donors. Finally, eligible donors will confirm whether they have diarrhea, fever, or other uncomfortable symptoms when submitting stool, as well as whether any cohabitants have diarrhea symptoms. The donor candidates recommended by the patients themselves will also need to pass all the screening processes mentioned above. Approximately 150–200 g of fresh stool provided by the eligible donors will be dissolved in 500 ml of sterile normal saline. The sample will be processed to filter out crude fiber, and 100% glycerol will be added to make the final glycerol concentration 10%. The sample will then be divided into 200-ml bottles (Corning Co., Ltd., NY, USA). This procedure will be performed under an anaerobic environment by replacing air with nitrogen gas in a glove box (SANPLATEC Co., Ltd., Osaka, Japan). The fecal suspension will be cryopreserved at −60°C in advance.

**Table 2A T2:** Donor exclusion criteria.

**Medical interview (exclusions)**
Age < 18 or >70
BMI < 18 or >25 or metabolic syndrome
Informed consent not provided
International travel to area with high risk of traveler's diarrhea in the last 6 months
High-risk sex (unprotected sex outside of a monogamous relationship in last 3 months, or men who have sex with men, sex for drugs or money)
Tattoo, body piercing, or acupuncture in the last 6 months
Needle stick accident in the last 6 months
Household members with active gastrointestinal infection
History of vaccination with a live attenuated virus in the last 3 months
Incarceration or a history of incarceration
**Medical history (exclusions)**
History of major gastrointestinal surgery
Family history of colorectal carcinoma
Active medical illness or symptoms
Antimicrobials (antibiotics, antivirals, antifungals), probiotics, or PPIs in the last 3 months
Taking any medications
Acute diarrhea in the last 3 months
Irritable bowel syndrome, chronic constipation, Chronic diarrhea Other intrinsic gastrointestinal illness: Inflammatory bowel disease, Colonic polyps, Colon cancer
Autoimmune disease
Atopic disease (including atopic dermatitis)
Chronic fatigue syndrome
**Psychiatric symptoms (exclusion)**
Any psychiatric disorder assessed by HAMD or NPI

*BMI, body mass index; PPIs, proton pump inhibitors; HAMD, Hamilton Depression Scale; NPI, Neuropsychiatric inventor*.

**Table 2B T3:** Donor screening criteria: blood test.

**Infections**
Hepatitis A virus IgM, Hepatitis B virus surface antigen/antibody, Hepatitis B virus core antibody, Hepatitis C virus antibody, Hepatitis E virus IgA
HIV type 1 and type 2 antibody and antigen
Human T-cell lymphotropic virus-1 antibody
Syphilis (RPR/TP)
Parasite-specific antibody screening test
Epstein Barr virus IgM
Cytomegalovirus antigen pp65 * RT-PCR
Tuberculosis (IFN-γ)
COVID-19 antigen
**Health condition**
Complete blood count
Electrolytes (sodium, potassium, chlorine)
Renal function tests (blood urea nitrogen, creatinine)
Liver function tests (AST, ALT, ALP, γ-GT)
Albumin
C-reactive protein

*Ig, immunoglobulin; HIV, human immunodeficiency virus; IFN, interferon; RPR, rapid plasma regain; TP, treponema pallidum; RT-PCR, reverse transcription-polymerase chain reaction; AST, aspartate transaminase; ALT, alanine transaminase; ALP, alkaline phosphatase; γ-GT, gamma-glutamyltransferase; SARS-CoV-2, severe acute respiratory syndrome corona virus 2*.

**Table 2C T4:** Donor screening criteria: fecal test.

Fecal occult blood testing
Parasites, ova, cysts
Cryptosporidium
Giardia
Norovirus
Rotavirus
General bacterial culture for common enteric pathogens
*Salmonella*
*Shigella*
*Yersinia*
*Campylobacter*
*Escherichia coli*
Diarrheagenic *Escherichia coli*
Enterohemorrhagic *Escherichia coli*
*Escherichia coli* verotoxin
*Clostridium difficile* toxin/ *Clostridium difficile*-specific GDH

*GDH, glutamate dehydrogenase*.

### Interventional Methods

First, eligible patients with UC will receive a combination antibiotic regimen called AFM comprising oral amoxicillin (1,500 mg/day), fosfomycin (3,000 mg/day), and metronidazole (750 mg/day). AFM will be administered to patients for 2 weeks until 2 days before the FMT (15). The fecal suspension (200 ml) will be thawed at 37°C using a water bath shaker on the day of the FMT operation. After bowel lavage using a standard polyethylene glycol (PEG) solution (Moviprep; EA Pharma, Tokyo, Japan), the patients will undergo total colonoscopy. A total of 200 mL of fecal suspension will be transferred to the patient's cecum. After the procedure, patients will receive scopolamine (10 mg) to slow intestinal transit and maintain a right lateral position. If the patient's drug dose for UC treatment has been stable for at least 12 weeks before the pre-registration, the patient will be permitted to continue ongoing treatment. However, changes in the dosage of drugs or initiation of new treatments will not be allowed during the intervention. After the A-FMT regimen described above, the patients will be randomized into two groups for a double-blind FMT post-treatment. One group will consume one bottle of alginate drink twice a day for 8 consecutive weeks, while the other group will take a placebo. The alginate drink is a mixed tea drink provided by Kaigen Pharma Co., Ltd. (Osaka, Japan) containing 4 g of sodium alginate per bottle (150 g) and has been proven to be safe (https://www.h-food.or.jp/dbadm/media/231cec6ad1478e2d429f733d93a7b272.pdf). The placebo uses the same tea drink with the sodium alginate removed and does not have a different appearance or taste. Patients can adjust their medication during post-observation after the study food intervention. To compare the effects of treatment, all patients will undergo symptom checking and colonoscopy and have blood and fecal samples tested at the times indicated in Table 3. Colonoscopy founding at screening, A-FMT and 8 weeks after study food intake should be taken video and judged by a third-part expert to confirm the scope and severity of UC lesions. Biopsy of inflammatory sites will be used to evaluate the histological score. Blood samples will be used to test routine blood biochemistry, and plasma components will be separated by centrifugal force and cryopreserved at −60°C. Fecal samples will be collected to determine the occult blood condition and calprotectin levels and analyze the intestinal microbiota and metabolites.

**Table 3 T5:** Protocol for sequential therapy of A-FMT with alginate drink or placebo.

[figure not shown]	**Screening stage**		**Duration of administration**				**Post-observation**
	**Pre-registration (within 2 months)**	**Screening (within a month)**	**AFM**	**A-FMT**	**Alginate drink or Placebo**		**6, 12, 18, and 24 months after**
			**2 weeks**		**4 weeks after**	**8 weeks after**	
Informed consent	•						
Check of patient background	•						
Administration of study food					•	•	
Check of symptoms	•	•		•	•	•	•
Endoscopy		•		•		•	
Blood samples		•		•		•	•
Fecal samples		•		•		•	•

*A-FMT, FMT following triple antibiotic therapy AFM (amoxicillin, fosfomycin, and metronidazole)*.

### Outcomes

The primary endpoint is to compare the changes in the Total Mayo Score at 8 weeks after study initiation and A-FMT from baseline between alginate intake group and placebo intake group. The secondary endpoints are the comparison of the following items at 8 weeks after study initiation and A-FMT from baseline:

The change in the Sum Endoscopic Mayo Score.Analysis of intestinal microbiota by 16S rRNA gene amplicon sequencing and whole-genome sequencing.Metabolomic analysis: In addition to SCFAs in stool samples, the amount of lipids, free fatty acids, bile acids, and other clinical markers will also be measured by liquid chromatography tandem mass spectrometry (35).

We will also do same analysis as (1), (2), and (3) at 6, 12, 18, and 24 months after 8 weeks post-study initiation.

Subpopulation analysis of the relationship between patients and donors is considered an exploratory endpoint.

Clinical features will be judged by the Total Mayo Score, and the mucosal appearance of the Mayo Score will be evaluated by endoscopy. To evaluate the overall status of the intestine, endoscopic findings will be evaluated using the Sum Endoscopic Mayo Score, which refers to the sum of the scores of the seven segments (appendicular region, cecum, ascending colon, transverse colon, descending colon, sigmoid colon, and rectum). Intestinal microbial analysis will assess changes in composition and diversity. Metabolomic analysis will evaluate the metabolites of microbiota and elucidate the mechanism of action of alginate in the treatment of UC.

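### The primary endpoint leaves its time origin and its baseline visit undefined; align it to the Table 3 study-food visit and adjust for the score taken at A-FMT

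*Protocol article*

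**What the plan says.** **Endpoint.** The Outcomes section makes this a comparison of "changes in the Total Mayo Score at 8 weeks after study initiation and A-FMT from baseline between alginate intake group and placebo intake group". In the abstract the same double anchor appears, in the plural: "The primary endpoints are the changes in the Total Mayo Score at 8 weeks after study initiation and A-FMT from baseline". It then describes the secondary comparison as one made "before and after 8 weeks of study food intake".

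**Sequence.** Interventional Methods puts the antibiotics first: "AFM will be administered to patients for 2 weeks until 2 days before the FMT". Randomisation comes later: "After the A-FMT regimen described above, the patients will be randomized into two groups for a double-blind FMT post-treatment". The randomised treatment follows: "One group will consume one bottle of alginate drink twice a day for 8 consecutive weeks".

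**Assessments.** The same section states: "Colonoscopy founding at screening, A-FMT and 8 weeks after study food intake should be taken video". Table 3 agrees. Endoscopy is marked at screening, at A-FMT and at one 8-week visit under the study-drink heading, and symptoms are checked at all three.

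**Follow-up.** The abstract counts 6 to 24 months from A-FMT. The Outcomes section repeats the secondary analyses "at 6, 12, 18, and 24 months after 8 weeks post-study initiation".

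**Sample size.** Sample Size Estimation assumes a difference of −2 and an SD of about 2.5 per group, with a two-sample t-test, and gives power of about 86.1%. It does not say which baseline the SD belongs to.

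**The concern.** A change-score endpoint needs a start point and an end point. Here the end point is counted from two events joined by a conjunction, one of them undefined, and the start point is called baseline without naming a visit.

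The baseline matters more because randomisation comes late. The antibiotics and the transplant are given to everyone before allocation. If baseline is screening, the measured change mixes what happened before randomisation with what happened under alginate or placebo. Only the second part can differ by treatment. The first part adds patient-to-patient variation to a comparison of about 30 per arm.

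An unnamed baseline also leaves room to choose between two legitimate analyses after the data are seen.

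**Working it through.** **1. The plan's own power.** Inputs: 60 patients at 1:1, so 30 per arm; difference 2; SD 2.5 (Sample Size Estimation); significance level 0.05 (Statistical Analysis), taken as two-sided.

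- Noncentrality = 2 / (2.5 × √(2/30)) = 3.10
- Critical t on 58 degrees of freedom = 2.002
- Power from the noncentral t = 86.1%

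The stated figure reproduces. A one-sided test would give 92.2%, so the two-sided reading is the right one.

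**2. The clock.** What each meaning of study initiation implies:

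| Meaning | Time to FMT | Week 8 falls |
|---|---|---|
| First antibiotic dose | 14 + 2 = about 16 days | 56 − 16 = day 40 after FMT |
| A-FMT | 0 | day 56 after FMT |
| First study drink | starts after A-FMT; interval not stated | day 56 of study drink |

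The article does not choose among these. The schedule does most of the work. The Total Mayo Score includes a mucosal item judged by endoscopy (Outcomes), and the only 8-week endoscopy is tied to study food (Interventional Methods, Table 3). The visit is therefore largely fixed, and the endpoint sentence is what fails to match it.

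**3. The follow-up clock.** Counting from A-FMT and counting from 8 weeks after study initiation do not agree. They differ by about 56 days if initiation is at or close to A-FMT, and by about 40 days if it is the first antibiotic dose. This conflict exists on all three readings in the table.

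**4. Candidate baselines.** Pre-registration has a symptom check but no endoscopy, so no Total Mayo Score can be formed there. Screening and A-FMT have both. A-FMT is the last scheduled assessment before randomisation. In Table 4 the baseline Total Mayo Scores fall into bands of 3–5 (8 patients) and 6–10 (25 patients). 8 + 25 = 33, so every patient lies inside the entry range of 3–10. That fits a screening value, but it is an inference and not a definition.

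**5. What the choice of baseline does.** Write S for the screening score, A for the A-FMT score and W for the week-8 score.

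- W − S = (W − A) + (A − S)
- A − S is fixed before randomisation, so its expected difference between arms is zero. There is no bias from this source.
- Var(W − S) = Var(W − A) + Var(A − S) + 2 Cov(W − A, A − S)

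The covariance can be negative, for example through measurement error in A. Simply moving the baseline to A-FMT is therefore not guaranteed to reduce the variance. Regressing W on both A and S avoids the problem. The two change scores are the special cases with slopes (0, 1) and (1, 0) on (A, S), so the best-fitting slopes cannot leave a larger residual variance than either. The price is 2 degrees of freedom, 58 to 56.

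**6. Illustration only.** If a share f of the variance of change were removed, SD = 2.5 × √(1 − f). With difference 2 and 30 per arm:

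| f (assumed) | SD | Power |
|---|---|---|
| 0 | 2.50 | 86.1% |
| 10% | 2.37 | 89% |
| 25% | 2.17 | 94% |
| 50% | 1.77 | 99% |

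The document gives no value for f.

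**The case against.** The best defence is that a reader with Table 3 in hand knows when the outcome is taken, that Table 4 shows what baseline means, and that change from entry is a legitimate estimand. Most of this stands. The visit is largely fixed, a screening baseline is balanced in expectation by randomisation, and the design is adequately powered on its own inputs. It is also fair that replacing the t-test changes the analysis with 33 patients already enrolled, and so is more than a correction of wording.

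Two parts do not stand. Table 4 only hints at the baseline. And the time point and baseline belong to the endpoint definition itself, which the article does state, with two anchors and a follow-up clock that conflicts with its own abstract. This is not detail left to a fuller document.

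Stronger readings are tempting and should be resisted:

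- A reader might infer that the two anchors really are 16 days apart. That holds only if study initiation is the first antibiotic dose, which the article never says. The abstract's description of the secondary endpoint points instead to the start of study food.
- A reader might go on to infer that the primary outcome is taken on day 40 of 56, scale the effect by 40/56, and report a large loss of power. No endoscopy is scheduled at that time, so no such Total Mayo Score is taken, and linear build-up of effect would be a further assumption.
- A reader might take the plural in the abstract to mean two primary time points, A-FMT and week 8. The Outcomes section speaks of a single primary endpoint, and a comparison at A-FMT would precede randomised treatment.

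**Conclusion.** The point holds as a defect of definition with an inexpensive gain in precision attached. Study initiation and baseline are undefined in the primary endpoint, and the follow-up anchor conflicts between the abstract and the Outcomes section. The 8-week visit can be recovered from the schedule. The baseline can only be guessed, with screening the likelier intention.

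If screening is meant, the comparison is valid but may be noisier than it need be, because it ignores a score already collected after the antibiotics and before allocation. The size of that loss cannot be stated. The SD of 2.5 is not tied to a baseline, and no correlation between visits is given. The figures of 89% to 99% rest on assumed variance shares and are not predictions. The sample-size calculation itself is not at fault.

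**What to change.** Amend before unblinding:

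1. Define the primary endpoint as the Total Mayo Score at the Table 3 visit 8 weeks after the start of study food, and delete study initiation as an anchor.
2. Name the baseline visit.
3. Compare arms by ANCOVA on the week-8 score, adjusting for the A-FMT-visit score with the screening score as a second covariate, in place of an unadjusted t-test on change. Because bowel lavage precedes the A-FMT colonoscopy, state that the symptom items for that visit refer to the days before lavage.
4. Apply the same clock and baseline to the secondary endpoints.
5. Choose one origin for the 6- to 24-month follow-up, and use it in the abstract, the Outcomes section and Table 3.

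No new visit or measurement is needed. There are two costs: change from before the whole regimen becomes a descriptive result, and the primary analysis differs slightly from the t-test used for the sample size. If the sponsor wants to keep screening as the baseline for reporting, the adjustment in item 3 can still be made.

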### Statistical Analysis

Relationships between Total Mayo Scores and Sum Endoscopic Mayo Scores will be assessed using a *t*-test. Furthermore, the correlation between the relative abundance of Bacteroidetes species using a Pearson's correlation coefficient will be evaluated. Differences will be considered significant at *P* < 0.05.

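### Bacteroidetes abundance is tested by a plain Pearson correlation at P < 0.05 although patients probably share donors, so false positives rise if both correlated variables cluster by donor

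*Protocol article*

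**What the plan says.** All places are in the protocol article.

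- **Donors:** "Approximately 150–200 g of fresh stool provided by the eligible donors will be dissolved in 500 ml of sterile normal saline". Glycerol is then added to a final concentration of 10%, and "The sample will then be divided into 200-ml bottles". The suspension is frozen ahead of use. Donors put forward by patients are allowed if they pass the same screening.
- **Interventional Methods:** "A total of 200 mL of fecal suspension will be transferred to the patient's cecum". The Introduction says of the regimen that "it only requires one FMT".
- **Introduction**, on the team's previous work: "Bacteroidetes species components in clinical responders treated with A-FMT remarkably resembled those of their donors".
- **Statistical Analysis:** "the correlation between the relative abundance of Bacteroidetes species using a Pearson's correlation coefficient will be evaluated", with significance set at P < 0.05. The second variable of the correlation is not named, and there is no donor term.
- **Outcomes:** "Subpopulation analysis of the relationship between patients and donors is considered an exploratory endpoint". No test or model is attached to this analysis.

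The article does not give the number of donors or of patients per donor. It also does not say whether bottles from one donation go to different patients.

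**The concern.** A Pearson P-value treats the 60 patients as 60 independent pairs of values. If one donor's stool goes into several patients, and a recipient's Bacteroidetes come to resemble the donor's, then recipients of the same donor resemble one another. If the variable on the other side of the correlation is also more alike within a donor, the standard error is too small and the test rejects too often.

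The Discussion builds the case for alginate largely on Bacteroidetes, so these correlations are likely to be read as evidence of mechanism. With a limited number of donors, one unusually good or poor donor could produce a nominally significant association that says little about Bacteroidetes in general.

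**Working it through.** **1. The plan's own figure.** Inputs from Sample Size Estimation: difference 2, SD 2.5, 60 patients at 1:1, so 30 per arm. Two-sided 5% is assumed, because sidedness is not stated. Noncentrality = 2 / (2.5 × √(2/30)) = 3.10 on 58 degrees of freedom, which gives power 86.1%. The stated figure reproduces, and donors do not enter it.

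**2. Bottles per donation.** Final volume = (500 ml + volume added by stool) / 0.9, because glycerol makes up 10%. The volume that stool adds after filtering is not given, so a range is used.

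| Stool adds | Final volume | 200-ml bottles |
|---|---|---|
| 0 ml | 500/0.9 = 556 ml | 2.8 |
| 150 ml | 650/0.9 = 722 ml | 3.6 |
| 200 ml | 700/0.9 = 778 ml | 3.9 |

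That is two full doses at the very least and three over most of the range, against one dose per patient.

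**3. False-positive rate of an unadjusted Pearson test.** With m patients per donor and intraclass correlations ICCx and ICCy for the two variables, the variance of the correlation is inflated by about

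D = 1 + (m − 1) × ICCx × ICCy,

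and the true error at nominal 5% is about 2 × [1 − Φ(1.96/√D)]. The documents give neither m nor any ICC; all of these are assumptions. The main case is m = 3, that is, 20 donors for 60 patients.

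| Case, m = 3 | D | Error by formula | Error by simulation |
|---|---|---|---|
| Abundance 0.5, outcome 0.1 | 1.1 | 6.2% | 6.2% |
| Abundance 0.5, outcome 0.2 | 1.2 | 7.4% | 7.4% |
| Abundance 0.5, outcome 0.3 | 1.3 | 8.6% | 8.7% |
| Donor-level variable (ICC 1), outcome 0.1 | 1.2 | 7.4% | 7.3% |
| Donor-level variable, outcome 0.2 | 1.4 | 9.8% | 9.7% |
| Donor-level variable, outcome 0.3 | 1.6 | 12.1% | 12.6% |
| One variable unclustered (0), other 0.3 | 1.0 | 5.0% | 5.1% |

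With one patient per donor, D = 1 and the error is 5% throughout.

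**4. Sensitivity to m.** At m = 2 the formula gives 5.6–6.8% for abundance (0.5) against outcome (0.1–0.3), and 6.2–8.6% for a donor-level variable. At m = 6, which would need donors to give more than once, simulation gives 11.0% and 22.6% for a donor-level variable at outcome ICC 0.1 and 0.3. The document does not support a particular value above three, so the conclusion does not rest on m = 6.

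**5. The randomised comparison.** Simulating the arm t-test with individual randomisation, m = 3 to 10 and outcome ICC 0.1 to 0.5, gives an error of 4.6% to 5.2%. There is no inflation, because each donor's recipients are randomised individually.

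**The case against.** The strongest reply is that much of this is inference, and that the model for an exploratory analysis normally sits in a full protocol or SAP that is not shown. Most of that reply stands, and it limits the point in five ways.

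- **Sharing is not stated.** A reader might infer from the bottle count that patients do share donors. The document makes this probable but does not say it, and a donor recommended by a patient may serve that patient only.
- **The patient-donor analysis is not shown to be wrong.** A reader might infer that it treats patients as independent, since the t-test and Pearson are the only methods named. Statistical Analysis does not apply either of them to it. The absence of a model in a condensed article is no error.
- **Pearson's second variable is not named.** If it does not cluster by donor, nothing is inflated. The Introduction reports resemblance to donors in responders only and gives no ICC for clinical outcome.
- **The effective sample size is not simply the number of donors.** That would hold only at an outcome ICC of 1. For a donor-level variable at m = 3 it is 60/(1 + 2 × ICC), or 50 at ICC 0.1 and 37.5 at ICC 0.3, not 20.
- **The arm comparison has no defect.** A donor term there could at most add some efficiency.

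What the reply does not remove is that Pearson at P < 0.05 is a stated choice, not a silence. The article's own preparation volumes and its own premise about donor resemblance make clustered data likely for that choice.

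**Conclusion.** The point holds in conditional form. If donors are shared and both correlated variables cluster by donor, the stated Pearson test exceeds its nominal 5%. Assuming three patients per donor, the error is about 6–9% for abundance (ICC 0.5) against outcome (ICC 0.1–0.3), and about 7–13% for a donor-level variable at the same outcome ICCs. The bottle arithmetic and the reported donor resemblance come from the document; the patients per donor and the ICCs are assumed. With one patient per donor, or with one variable unclustered, there is no inflation.

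Severity is low. The affected results are exploratory or supportive. The primary endpoint, its 5% error and the 86.1% power are untouched. The document does not support a broader claim that the plan's analyses as a whole give too many significant results.

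**What to change.** In Statistical Analysis:

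- State that the donor identifier is recorded for every patient, and that the number of donors and of patients per donor will be reported.
- Take the P-values for the Bacteroidetes correlations from a model with a donor random intercept. Pearson's coefficient can stay as a descriptive summary.
- Apply the same rule to any test in the exploratory patient-donor analysis under Outcomes. For features of the donor, permutation at donor level is an alternative.
- If neither is done, report these results descriptively, without P-values.

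A donor term in the comparison of alginate with placebo is optional.

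The cost is a change of wording and a little more programming. The planned patient-donor analysis needs the donor link anyway. Some exploratory P-values will become larger. If it turns out that each donor served a single patient, the ordinary Pearson test is adequate on this point and a sentence saying so is enough.
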